## Abstract

**Background: **
*Chlamydia trachomatis*,
*Neisseria gonorrhoeae*,
*Trichomonas vaginalis* and bacterial vaginosis have been associated with preterm birth and low birth weight, and are highly prevalent among pregnant women in many low- and middle-income settings. There is conflicting evidence on the potential benefits of screening and treating these infections in pregnancy. Newly available diagnostic technologies make it possible, for the first time, to conduct definitive field trials to fill this knowledge gap. The primary aim of this study is to evaluate whether antenatal point-of-care testing and immediate treatment of these curable sexually transmitted and genital infections (STIs) leads to reduction in preterm birth and low birth weight.

**Methods**: The Women and Newborn Trial of Antenatal Interventions and Management (WANTAIM) is a cluster-randomised crossover trial in Papua New Guinea to compare point-of-care STI testing and immediate treatment with standard antenatal care (which includes the WHO-endorsed STI ‘syndromic’ management strategy based on clinical features alone without laboratory confirmation). The unit of randomisation is a primary health care facility and its catchment communities. The primary outcome is a composite measure of two events: the proportion of women and their newborns in each trial arm, who experience either preterm birth (delivery <37 completed weeks of gestation as determined by ultrasound) and/or low birth weight (<2500 g measured within 72 hours of birth). The trial will also evaluate neonatal outcomes, as well as the cost-effectiveness, acceptability and health system requirements of this strategy, compared with standard care.

**Conclusions: **WANTAIM is the first randomised trial to evaluate the effectiveness, cost-effectiveness, acceptability and health system requirements of point-of-care STI testing and treatment to improve birth outcomes in high-burden settings. If the intervention is proven to have an impact, the trial will hasten access to these technologies and could improve maternal and neonatal health in high-burden settings worldwide.

**Registration: **
ISRCTN37134032.

## Introduction

### Background

Every year there are an estimated 2.6 million stillbirths and 2.6 million neonatal deaths globally; the majority are in low- and middle-income countries (LMIC), primarily in remote and rural communities
^1^. Papua New Guinea (PNG) has among the highest neonatal mortality ratios worldwide, with an estimated 25 per 1000 live births in 2013, compared with a global figure of 18
^2,
3^. Preterm birth and low birth weight are closely linked, as well as being independent and major contributors to neonatal mortality. Together, they affect around 20% of newborns in PNG
^4^. The causes of preterm birth and low birth weight are diverse, but a range of infections including malaria, syphilis, and other sexually transmitted and genital infections (STI) have been implicated
^5–
10^. In many resource-limited countries, poor access to antenatal care means that opportunities for early diagnosis and clinical intervention of such infections are missed
^11^.

Research studies among antenatal women in a number of LMIC have found extremely high rates of infection with genital STIs, particularly gonorrhoea, chlamydia, trichomonas and bacterial vaginosis, which are readily curable with cheap antibiotics
^5^. In PNG, pregnant women have among the highest prevalence of these infections of any developing country
^12^. In the country’s first bio-behavioural survey of STIs in pregnancy, we found that the prevalence of chlamydia was 23%, gonorrhoea 14%, and trichomonas 22%, with 44% of women having at least one of these infections
^13^. Similar levels of infection were found in a pilot study of antenatal point-of-care STI testing and treatment conducted by our group
^14^ in which 54% of women had one or more of chlamydia, gonorrhoea, trichomonas or BV, and the prevalence of each of these STIs was 19%, 11%, 38%, and 18%, respectively. Similar STI prevalences were also observed in an earlier randomised trial of malaria prevention in pregnancy
^15^. In all of these studies, between 65–80% of infections among antenatal women were asymptomatic.

### STIs and adverse birth outcomes

Gonorrhoea, chlamydia, trichomonas and bacterial vaginosis have been linked to adverse birth outcomes. The precise pathogenesis remains unclear, with postulated mechanisms including direct infection of the foetus; stimulation of foetal inflammatory responses; excessive maternal immunogenic reactions; or a combination of factors
^16^. There is evidence that gonorrhoea and chlamydia are associated with both preterm birth and low birth weight
^5,
8,
9,
17–
23^, as well as miscarriage
^5,
21^, stillbirth
^5,
24^, premature rupture of membranes
^5,
17,
25^, postpartum endometritis
^5^ and ophthalmia neonatorum
^5^. The reported strength of association varies across studies and endpoints
^8,
26^. In a meta-analysis, we found that trichomonas is associated with a relative risk of 1.4 (95%CI: 1.1-1.7) for preterm birth
^27^, and is also linked to low birth weight and premature rupture of membranes. Bacterial vaginosis is strongly associated with preterm birth and other adverse outcomes
^17,
20,
28^. The population attributable risk of these infections as causes of adverse birth outcomes depends on their underlying population prevalence. For preterm birth, estimates have ranged from 15% for gonorrhoea, chlamydia, trichomonas and bacterial vaginosis individually, and up to 42% for a combination of one or more of these infections
^9,
19,
20^.

### Management of STIs in pregnancy

Diagnosis of genital infections has traditionally relied upon microscopy, culture, and/or serology, all of which require technical expertise and laboratory services which are not widely available in most resource-limited settings. Accordingly, in the 1990s, the World Health Organization (WHO) developed a syndromic management strategy for diagnosing genital infections that uses clinical presentation without laboratory confirmation to make treatment decisions. Syndromic management, however, cannot identify asymptomatic infections, which might contribute to its limited impact on disease prevalence
^12,
29^. The development and introduction of nucleic acid amplification test (NAAT) technologies in the 1990s provided commercially available laboratory systems, which are highly accurate, robust for the detection of
*C. trachomatis*,
*N. gonorrhoeae* and
*T. vaginalis* in both urine and genital swabs, and have relatively short turnaround time. The costs and technical requirements of these platforms however have meant that they are not routinely available in resource-limited settings. In addition, despite the recognised consequences of gonorrhoea, chlamydia, trichomonas and bacterial vaginosis in pregnancy, there has been no consensus as to whether it is beneficial to offer antenatal screening and treatment for these infections. Authorities in Australia
^30^, and the United States
^31,
32^ recommend antenatal screening for chlamydia in all women under 25 years of age, but routine screening for asymptomatic gonorrhoea, trichomonas and bacterial vaginosis is not currently recommended, except for settings of increased risk, such as in remote Aboriginal communities in Australia.

In the absence of accurate diagnostic tests for STIs in high-burden, low-resource settings, presumptive strategies that do not depend on knowing a woman’s true infection status have been considered. A randomised trial of single dose presumptive STI treatment (1 g azithromycin, 400 mg cefixime and 2 g metronidazole) among pregnant women in Uganda found significant reductions in low birth weight and neonatal death
^33^, but a subsequent sub-analysis found excesses of the same outcomes in the treatment arm among the infants of women who were retrospectively determined to have had trichomonas
^34^. This finding was consistent with an earlier trial in which women were presumptively given 2 g metronidazole twice during their pregnancy
^35^ and which found an increase in low birth weight; but not with another that used the same metronidazole dosing regimen to treat women with microscopically-confirmed bacterial vaginosis and found no such effect on birth weight
^36^. Conversely, in a field trial of 300mg clindamycin twice daily for 7 days for microscopically-confirmed bacterial vaginosis, the risk of preterm birth among women with bacterial vaginosis in the intervention phase was half that of women with this condition in the pre-intervention phase (RR 0.5; 95% CI: 0.3-0.9)
^28^. In contrast to earlier research that suggested treatment for trichomonas in pregnancy might increase the risk of adverse birth outcomes (hypothesized to be the result of dying trichomonads releasing inflammatory mediators thereby inducing preterm labour)
^31,
37^, a trial among 2428 women in South Africa found no association between oral metronidazole treatment and preterm birth among women diagnosed with trichomoniasis
^38^; as did a recent retrospective cohort study among over 4000 women in the United States
^39^. Faced with this conflicting body of scientific evidence, recent reviews have concluded that there is insufficient evidence to inform policy on STI testing and treatment in pregnancy, and that field trials are needed to confirm or refute earlier findings on the potential risks and benefits
^31,
32,
40^.

New point-of-care diagnostic technologies for STIs have become available in the last 5 years and make it possible for the first time to conduct such trials in high-burden, low-resource settings. Following the successful implementation of point-of-care devices for the rapid diagnosis of syphilis and HIV, there was an effort to use similar strategies, generally based on lateral flow technology, for chlamydia, gonorrhoea and trichomonas testing, but the results were disappointing, largely due to poor sensitivity
^41–
46^. In the past 5 years, there has been a major breakthrough in rapid diagnosis of STIs. A fully automated portable NAAT platform (GeneXpert, Cepheid, Sunnyvale, CA) can perform tests for
*C. trachomatis*,
*N. gonorrhoeae* and
*T. vaginalis* that are as accurate as laboratory-based NAATs
^47–
50^. This platform has substantially improved the diagnosis and management of tuberculosis in many low- and middle-income settings, including PNG
^51^. Disposable cartridges hold the reagents including primers and probes for the simultaneous detection of chlamydia and gonorrhoea, with a separate cartridge used for trichomonas detection. Test results are available in approximately 90 minutes for Xpert CT/NG and 60 minutes for the Xpert TV test. Building on the experience from the Test Treat ANd GO (TTANGO) Trial
^52^ in remote Aboriginal communities in Australia, we showed the feasibility of point-of-care STI testing and treatment in a pilot study in selected antenatal settings in PNG
^52,
53^. The diagnosis of bacterial vaginosis has until recently relied on Amsel’s clinical criteria, or on highly skilled, time-consuming microscopic examination of Gram stained vaginal smears using the Nugent score
^53–
55^. The BVBlue test (OSOM BVBlue Test, Gryphus Diagnostics, USA) is a chromogenic test based on the detection of increased vaginal fluid sialidase activity
^56^. It is the first robust point-of-care test available for the diagnosis of bacterial vaginosis and, in previous evaluations, had high sensitivity (90%) and specificity (95%) compared with clinical and laboratory criteria
^56,
57^.

### Significance and potential impact of the trial

Women in LMIC worldwide experience a high burden of adverse birth outcomes. The body of available scientific evidence about the effect of testing and treatment for STIs and other genital infections in pregnancy is conflicting. Recent reviews have concluded that there is insufficient evidence to inform policy on STI testing and treatment in pregnancy, and that field trials are needed to confirm or refute earlier findings on the potential risks and benefits
^31,
32,
40^. If we show a benefit for antenatal point-of-care STI testing and treatment, our findings could hasten access to these technologies and thereby lead to improved maternal and neonatal health. If no benefit is found, resources for maternal and neonatal health care can be directed elsewhere.

## Protocol

### Trial aim and objectives

The overall aim of the Women And Newborn Trial of Antenatal Interventions and Management (WANTAIM) is to measure the effectiveness, health system implementation requirements, cost-effectiveness and acceptability of antenatal point-of-care STI testing and immediate treatment to improve birth outcomes in high-burden, low-income settings. 

*Primary Objective*

1. Evaluate whether point-of-care testing and immediate treatment of curable STIs in pregnancy leads to a reduction in preterm birth and/or low birth weight compared with standard antenatal care.

In this trial, ‘curable STIs’ includes
*C. trachomatis*,
*N. gonorrhoeae*,
*T. vaginalis* and bacterial vaginosis, all of which will be tested for and treated at point-of-care in the intervention arm.

*Secondary Objectives*

1. Evaluate whether point-of-care STI testing and treatment in pregnancy leads to an increase in mean birth weight compared with standard antenatal care;

2. Evaluate whether point-of-care STI testing and treatment in pregnancy leads to a reduction in premature rupture of membranes compared with standard antenatal care;

3. Evaluate whether point-of-care testing in pregnancy increases the diagnosis and treatment of STIs compared with symptom-based ‘syndromic’ management;

4. Evaluate the cost-effectiveness of point-of-care STI testing and treatment in pregnancy compared with standard antenatal care;

5. Evaluate the health system implementation requirements of point-of-care STI testing and treatment in pregnancy compared with standard antenatal care;

6. Evaluate the acceptability of antenatal point-of-care STI testing and treatment compared with standard care;

7. Evaluate whether point-of-care STI testing and treatment in pregnancy leads to a reduction in neonatal eye infection and/or pneumonia compared with standard antenatal care (
*among a sub-set of 2000 participants only*);

8. Evaluate mother-to-child transmission of
*C. trachomatis* and
*N. gonorrhoeae* (
*among a sub-set of 2000 participants only*);

9. Evaluate the performance of the Xpert
^TM^ CT/NG Test for the diagnosis of neonatal eye infection and pneumonia using ocular and nasopharyngeal specimens (
*among a sub-set of 2000 participants only*).

### Trial outcome measures

*Primary*

The primary outcome is a composite measure of two events, the proportion of women and their newborns in each trial arm who experience either:

a) preterm birth (live birth before 37 weeks’ gestational age as estimated by ultrasound examination at 26 weeks’ gestational age or earlier, adjusted according to reported date of last menstrual period in accordance with trial standard operating procedures); and/or

b) low birth weight (birth weight <2500 g measured as soon as possible after birth using calibrated, medical-grade infant weighing scales accurate to within 10 g; birth weights measured within 72 hours of birth only will be included in the primary outcome).

*Secondary*

The trial secondary outcome measures are:

1. Mean birth weight among newborns in the control and intervention arms of the trial;

2. Proportion of women who experience premature rupture of membranes (defined as membrane rupture before the onset of labour);

3. Number of curable STIs diagnosed and treated;

4. Incremental cost effectiveness ratios (cost per preterm birth and/or low birth weight case averted; cost per STI diagnosed and treated; cost per life year saved; cost per disability-adjusted life year (DALY) averted);

5. Health system implementation requirements;

6. Acceptability of antenatal point-of-care STI testing and treatment among (a) women and (b) health workers.

7. Proportion of newborns with an eye infection or moderate/severe pneumonia by 4–6 weeks postnatal (
*among a sub-set of 2000 participants only*);

8. Incidence of mother to child transmission of
*C. trachomatis* or
*N. gonorrhoeae* as indicated by positive newborn eye (
*C. trachomatis* or
*N. gonorrhoeae*) or nasopharyngeal (
*C. trachomatis*) swabs by 4–6 weeks postnatally (
*among a sub-set of 2000 participants only*);

9. Diagnostic test accuracy (sensitivity, specificity, positive and negative predictive values) of Xpert CT/NG Test compared with laboratory-based polymerase chain reaction (PCR) assays (
*among a sub-set of 2000 participants only*).

The health economics and health systems implementation components of the trial will be described in detail in separate protocol papers.

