### Statistical analysis

The statistical analysis plan for the trial will be presented in detail in a separate manuscript.

All analyses (including the cost-effectiveness analysis) will be conducted using methods that take into account the cluster-randomised cross-over design. All analyses will be carried out using the latest available version of Stata statistical software (15.0 or above; College Station, TX, USA).

Primary data analysis will be by intention to treat (ITT) at the cluster level, meaning that all participants with a recorded outcome will be included in the analysis, and will be analysed according to the treatment group to which they were randomised; and all clusters will be included in the analysis according to the treatment group to which they were randomised. Initial analyses will be unadjusted comparisons of intervention and control clusters. If there appear to be any important imbalances between randomised groups in terms of baseline demographic characteristics, risk factors for low birth weight and/or preterm birth, and the prevalence of specific STIs, adjusted analyses will be performed, and presented in addition to unadjusted comparisons.

Effect measures, comparing outcomes between intervention and control clusters, will be estimated with 95% confidence intervals and p-values from the corresponding hypothesis tests. The effect measure for the primary outcome will be a risk ratio, defined as the ratio between the proportion recorded as having the outcome of interest in the intervention arm, and the corresponding proportion in the control arm.

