### Data and Safety Monitoring Board (DSMB)

The DSMB will oversee the trial and be comprised of senior researchers in maternal and child health, trial statisticians and provincial and national policy makers working in maternal health in PNG. The DSMB will provide expert advice and guidance to the TSC and will review primary trial outcome data every 4–6 months, including the possibility that point-of-care STI testing and treatment may be enhancing rather than reducing adverse birth outcomes. The DSMB will also review all SAE Reports. The DSMB will review incidence rates in the different study arms and advise the TSC on any revision of the sample size required during the course of the trial. Meetings will be coordinated by the Chief Investigator, and the Trial Statistician will supervise and prepare the tables in the format approved by the DSMB.

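### The primary outcome is defined in incompatible ways, so whether a stillbirth counts depends on the reading, and no secondary outcome counts fetal loss as such

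*Protocol article*

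**What the plan says.** The abstract (Methods) defines the first component as "preterm birth (delivery <37 completed weeks of gestation as determined by ultrasound". The formal definition under Trial outcome measures, Primary, item (a), is narrower: "preterm birth (live birth before 37 weeks" of gestational age. Item (b) is "low birth weight (birth weight <2500 g measured as soon as possible after birth", with only weights taken within 72 hours counting. It carries no live-birth condition. The stem covers "the proportion of women and their newborns in each trial arm who experience either" of these events, and newborn is not defined as live-born.

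Other sections bear on the same question:

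- Sample size gives the planning rate of 18% per pregnancy, not per live birth.
- Statistical analysis says that "all participants with a recorded outcome will be included in the analysis", without saying whether a stillbirth or miscarriage is a recorded outcome.
- STIs and adverse birth outcomes associates gonorrhoea and chlamydia with preterm birth and low birth weight, "as well as miscarriage" and stillbirth.
- None of the nine secondary outcomes counts miscarriage or stillbirth. Both are classed as serious adverse events in Box 1.
- The DSMB section asks the board to consider whether the intervention "may be enhancing rather than reducing adverse birth outcomes", on primary outcome data. It also gives the board all serious adverse event reports.

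**The concern.** A primary outcome needs one event rule and one denominator. Here the abstract and item (a) disagree, and items (a) and (b) do not match within the formal definition itself. The difference cannot be put down to a shortened abstract alone.

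Two things are at stake. First, if item (b) is applied as written, a small stillbirth is an event only if someone weighed it in time. The Rationale under Trial design and setting accepts that the intervention cannot be blinded, so an event rule that rests on whether a stillborn baby was weighed is poorly protected.

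Second, fetal loss competes with the outcome. Under a live-birth reading, a pregnancy that moves from early live birth to fetal loss leaves the event count, and one that moves the other way enters it. If treatment affects fetal loss in either direction, the live-birth composite alone does not show what happened to all pregnancies.

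**Working it through.** **Step 1: the readings side by side.**

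| Pregnancy outcome after enrolment | Abstract | Item (a) | Item (b) as written | Item (b) if newborn means live-born |
|---|---|---|---|---|
| Preterm stillbirth | event | no event | event if <2500 g and weighed within 72 h | no event |
| Term stillbirth <2500 g | not preterm; event only by weight | no event | event if weighed within 72 h | no event |
| Miscarriage | event if read literally (no lower gestational limit) | no event | only if treated as a birth and weighed | no event |
| Term stillbirth ≥2500 g | no event | no event | no event | no event, or outside the denominator |

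The first three rows change status with the reading. The fourth may still change the denominator.

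**Step 2: the plan's target (Sample size).** Control risk is 18% and the relative reduction about 23%. The difference is 0.18 × 0.23 = 0.0414, or 4.14 points. The intervention risk is 0.18 − 0.0414 = 0.1386, so RR = 0.77.

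**Step 3: equal fetal loss in both arms.** The documents give no local loss rate. Assume loss of 2–5% after enrolment, 80% of it before 37 weeks or under 2500 g, and risks of 18% and 13.86% among live births. With loss s, the risk counting qualifying losses is (1 − s) × p + 0.8 × s.

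- s = 2%: control 0.98 × 0.18 + 0.016 = 0.1924; intervention 0.98 × 0.1386 + 0.016 = 0.1518. Difference 4.06 points, RR 0.79.
- s = 5%: control 0.95 × 0.18 + 0.04 = 0.2110; intervention 0.95 × 0.1386 + 0.04 = 0.1717. Difference 3.93 points, RR 0.81.

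The RR therefore moves by about 0.02–0.04 under these assumptions. For stillbirth only, at an assumed 1–3% with 50–90% qualifying, the same formula gives RR 0.78–0.80, a shift of about 0.01–0.03.

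**Step 4: unequal loss, live-birth RR held at 0.77.** Assume 2% stillbirth in control, 80% qualifying.

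- Intervention stillbirth 1%: (0.99 × 0.1386 + 0.008) / 0.1924 = 0.75.
- Intervention stillbirth 4%: (0.96 × 0.1386 + 0.032) / 0.1924 = 0.86.

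**Step 5: illustration of a misleading live-birth result.** Take 2% loss in control and no true benefit. In the intervention arm, move 10 per 1000 pregnancies from preterm or low-weight live birth to fetal loss. Control events are 0.98 × 0.18 = 0.1764 of pregnancies; intervention events are 0.1764 − 0.01 = 0.1664.

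- Losses excluded from the denominator: 0.1664 / 0.97 = 17.15% against 18%. Apparent benefit 0.85 points, RR 0.95; 0.85 / 4.14 is about 20% of the target.
- Losses kept in the denominator: 16.64% against 17.64%. Apparent benefit 1.0 point; 1.0 / 4.14 is about 24% of the target.
- Composite of fetal loss, preterm birth or low birth weight: control 0.1764 + 0.02 = 0.1964; intervention 0.1664 + 0.03 = 0.1964. No difference, which is the true position in this example.

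**The case against.** The best defence is that the outcome section governs over the abstract, that the stem speaks of newborns, and that item (b) refers to infant scales, so live births for both components is the natural reading. That is a fair guess at intent. But newborn is undefined, and item (a) adds a live-birth condition that item (b) lacks, so the text does not settle it.

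It can also be said that denominators, supportive analyses and tables of fetal loss belong in the separate statistical analysis plan. That is right for their detail, and their absence here is not the point. The event definition is the protocol's own statement, and it conflicts with itself.

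Several stronger readings are tempting and not supported:

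- A reader might infer that fetal loss lies outside every efficacy outcome. That is complete only under the live-birth reading; under the abstract or item (b) as written, some losses enter as preterm or low-weight events.
- A reader might infer that fetal loss goes unwatched. It does not: losses are reported as serious adverse events, the DSMB reviews all such reports, and the Trial Steering Committee reviews adverse birth outcomes about twice a year. What is not stated is a comparison of fetal loss between arms.
- A reader might take all four infections to be linked to miscarriage and stillbirth. The protocol names those outcomes for gonorrhoea and chlamydia only.
- On the Step 3 assumptions, 2000 × 0.02 × 0.8 = 32 to 2000 × 0.05 × 0.8 = 80 women per arm could change status. It is tempting to set this beside the target of 0.0414 × 2000 = 83 events. But the first is a count within each arm and the second a difference between arms; equal losses largely cancel.
- Step 5 needs loss to rise from 2% to 3%, a 50% relative increase, entirely among pregnancies otherwise bound to be preterm or low weight. Nothing in the documents says this will happen. Nor do they suggest that weighing of stillbirths will differ by arm; postnatal procedures are otherwise meant to be the same in both.

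**Conclusion.** The inconsistency is real, sits in current text and concerns the primary outcome. A preterm or low-weight stillbirth is an event or not depending on which sentence is followed and, under item (b) as written, on whether it was weighed within 72 hours.

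The size is modest if fetal loss is equal between arms: the 4.14-point target becomes about 4.06–3.93 points with 2–5% loss and 80% qualifying. It matters mainly if treatment changes fetal loss, or if weighing of stillbirths differs by arm. In the illustration, a live-birth composite shows a spurious benefit of 0.85–1.0 points, about 20–24% of the target. All loss rates and qualifying shares are assumptions. The calculations show what could happen and are no estimate of an expected bias.

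**What to change.** Reconcile the abstract and items (a) and (b) to one birth-status rule applied to both components: live births only, or all births. State the matching denominator, including how women with a miscarriage or stillbirth are handled. If all births are counted, give the gestational age from which a loss counts as a birth.

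If live births only is kept, pre-specify one supportive analysis, by the same method as the primary: fetal loss after enrolment, preterm birth or low birth weight, among all women with a known pregnancy outcome. Compare miscarriage and stillbirth by arm from the serious adverse event data.

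The cost is wording and one extra analysis. No new data collection or change in sample size is needed.
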